## Ethics and dissemination

### Adverse event reporting

As the trial is conducted, any serious adverse events (SAE; all serious undesired events independent of whether they have a suspected relationship to the intervention) or suspected unexpected serious adverse reactions (SUSAR; a serious adverse event which is suspected to be related to some part of the intervention) will be recorded. Any SUSAR will be reported to the ethics committee within 15 days of the investigators becoming aware of the event. After two SAE/SUSAR in a row, the trial will be paused and continuation will be evaluated.

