## Study objectives

### Primary objective

The primary objective of this study is to determine whether the intervention is feasible to administer and acceptable to participants. This objective includes an assessment of whether the FutureU for Mental Health intervention was sufficient to establish a sense of realism, i.e., engagement with the virtual environment and embodiment of the virtual avatar.

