##### Sample size

As this trial is primarily to establish feasibility, acceptability, and proof of concept, a full power analysis is not appropriate. However, to be able to assess feasibility process outcomes, we target recruitment at sixty participants (*n* = 60), with *n *= 40 receiving the intervention. There is no consensus on sample size of pilot studies – recommendations range from 12 [31] to 50 [32]. This sample size of *n* = 60 is in line with multiple best practice recommendations for feasibility trials and it is suggested that a sample of 30 in the intervention arm is sufficient for the main aims of this pilot study: to adequately establish feasibility and to interpret qualitative measures of acceptability [33, 34].

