### Interventions

Three interventions will be administered. First, as a treatment as usual control (TAU), a Coping Plan is administered by the experimenter during the first in-person session to all participants. Next, participants in the treatment condition (TX) will all receive the Self-Help Intervention (SH) and the Positive Future Memories Intervention (PFM)—collectively known as the FutureU for Mental Health (FU-MH) Intervention. Participants in the TX condition will be assigned to either group A or B, which will dictate the order in which the SH and PFM interventions are received. Group A will first receive SH and then PFM; Group B will first receive PFM and then SH.

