Feasibility: Virtual Reality Engagement and Embodiment

(i)Embodiment in AvatarParticipants will complete a measure adapted from Banakou et al. 37 which assesses the degree to which participants experience the virtual avatar as their own body. The scale contains four items, each rated on a response scale of 1 = Strongly Disagree to 4 = Strongly Agree. Scores are determined by averaging responses to each item. Item three is reverse coded.(ii)Proteus EffectParticipants will complete a measure developed by van Gelder et al. 4 which assesses the degree to which people take over the characteristics associated with the avatar they embodied. The scale contains three items, each rated on a response scale of 1 = Strongly Disagree to 4 = Strongly Agree. Scores are determined by averaging responses to each item.(iii)PresenceParticipants will complete a measure adapted from Hartmann et al. 38 to assess the degree to which participants have the feeling they were actually present in the virtual environment, i.e., a shift in users’ self-location. The scale contains four items, each rated on a response scale of 1 = Strongly Disagree to 4 = Strongly Agree. Scores are determined by averaging responses to each item.(iv)EngagementParticipants will complete a measure adapted from O’Brien et al. 39 to assess the degree to which the participant feels engaged in the task in virtual reality. The scale contains fourteen items, each rated on a response scale of 1 = Strongly Disagree to 4 = Strongly Agree. Scores are determined by averaging responses to each item. Items 4, 5, and 6 are reverse coded.(v)Avatar RecognitionParticipants will complete a measure developed by van Gelder et al. 40 which assesses the degree to which participants can identify and recognize themselves in the avatar of their future self. The scale contains seven items, each rated on a scale of 1 = Strongly Disagree to 7 = Strongly Agree. Scores are determined by averaging responses to each item.

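### Adverse event recording is stated for serious events only, so the pilot cannot report a rate of non-serious reactions to its two VR sessions

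*Protocol article*

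**What the plan says.** Under Adverse event reporting, two classes of event are to be recorded. The first is "any serious adverse events (SAE; all serious undesired events independent of whether they have a suspected relationship to the intervention"). The second is the SUSAR, defined as "a serious adverse event which is suspected to be related to some part of the intervention) will be recorded". Both are restricted to serious events, and so is the rule that follows: "After two SAE/SUSAR in a row, the trial will be paused and continuation will be evaluated".

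The Primary objective is to "determine whether the intervention is feasible to administer and acceptable to participants", including whether the VR gave a sufficient sense of realism. Under Outcomes measures, the block titled "Feasibility: Virtual Reality Engagement and Embodiment" lists embodiment, Proteus effect, presence, engagement and avatar recognition. Acceptability is measured by AIM, IAM and FIM and by an investigator-developed survey of satisfaction and feedback. Table 1 places the engagement/embodiment and the acceptability scales at t2 and t3, in the treated groups.

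On exposure, Sample size says "we target recruitment at sixty participants", with "40 receiving the intervention". Each treated participant has two VR sessions of about 30 minutes (Table 1): "Group A will first receive SH and then PFM; Group B will first receive PFM and then SH".

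Table 2 rests progression on feasibility and acceptability. Its VR row uses embodiment, engagement and recognition. Its acceptability row is a judgement without a numeric threshold, drawing on data from participants and experimenter.

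**The concern.** The new element of this trial is the pair of headset sessions. In one, a participant with depressive symptoms faces and then embodies a distressed likeness of themselves; in the other they embody a self aged by ten years. The foreseeable undesired reactions are mostly non-serious: feeling unwell, discomfort, being upset, wanting to stop. These fall outside both recorded classes.

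A pilot whose main question is whether a VR intervention is feasible and acceptable would normally hand its successor a figure for how often participants reacted badly to it. Under the rule as written, a Go on the VR and acceptability rows of Table 2 can be reached without that figure, and the full trial would be planned without it.

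**Working it through.** The point concerns what is collected, and the article states no tolerability figure to reproduce. Its only computed interval is the Wilson interval for 85% retention at n = 60 (Table 2). With p = 51/60 = 0.85 and z = 1.96:

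- centre = (0.85 + 3.84/120) / (1 + 3.84/60) = 0.829
- half-width = 1.96 × √(0.85 × 0.15/60 + 3.84/(4 × 60²)) / (1 + 3.84/60) = 0.090
- interval = 73.9% to 91.9%, which matches the stated 74–92%.

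That figure is correct and does not bear on this point.

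**Could any planned source give a count of non-serious VR reactions?**

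- *SAE and SUSAR records*: no, serious events only.
- *VR scales*: as described, they measure realism, engagement and self-recognition, not symptoms.
- *AIM, IAM, FIM*: averaged implementation ratings. A low score may reflect a bad reaction but does not identify one.
- *Satisfaction and feedback survey*: a reaction may be mentioned, but no fixed question about reactions is described, so the absence of a mention cannot be read as the absence of a reaction.
- *PANAS*: due at every measurement point, with assessments before and after each session. It quantifies a shift in affect, but has no physical symptoms and does not tie a shift to headset or avatar.
- *C-SSRS*: baseline, before sessions and at follow-up; suicidal ideation only.
- *Completion and drop-out*: counted with a denominator, with reasons only if volunteered. A participant who felt unwell but finished does not appear.
- *Experimenter input to Table 2*: informs a judgement, with no stated tally.

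**Is the sample large enough for a count to be useful?** Inputs: n = 40 treated (Sample size); reaction rates of 5% and 10%, which are assumptions because the article gives none.

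- P(at least one affected) = 1 − (1 − rate)^40
- at 5%: 1 − 0.95^40 = 0.87, with 2 participants expected; a count of 2/40 has a Wilson 95% CI of 1% to 17%
- at 10%: 1 − 0.90^40 = 0.985, with 4 expected; 4/40 has a CI of 4% to 23%
- none in 40: one-sided 95% upper bound 1 − 0.05^(1/40) = 7.2%; two-sided, 1 − 0.025^(1/40) = 8.8%

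If only 34 contributed data (0.85 × 40, borrowing the retention target), the one-sided bound for zero events would be 1 − 0.05^(1/34) = 8.4%. The sample size does not stand in the way of an informative count.

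**The case against.** The strongest reply is that tolerability is not left unobserved. PANAS before and after each VR part bears directly on being upset. Completion of all sessions is counted, and the CONSORT diagram is to show when participants left and, if known, why, so someone who stops and does not finish is visible. The acceptability scales follow each VR part and are described separately for SH and PFM. A clinically trained experimenter runs every session and contributes to the acceptability judgement. All of this stands. A reader might infer that the trial gathers no tolerability data, or that a non-serious reaction could never come to light; the article does not support either reading.

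A second reply is that the section is short, does not say that non-serious events are excluded, and may condense a fuller safety section. Nor are the questionnaire items printed, so it cannot be shown that no item touches on discomfort. This too has force: the point is about the rule and the measures as described, not a proven absence elsewhere. It does not remove the point, because the article does state which events will be recorded and describes its measures down to item counts and reverse coding, yet nothing on feeling unwell appears among them.

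A third reply is that the article plans no adverse event table, so a misreading of an empty one is conjecture. Agreed; the point does not rely on it.

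**Conclusion.** The point holds as a gap in systematic recording. The stated rule covers serious events only, and no described measure fills the space for reactions among participants who complete a session. The pilot will therefore have indirect signals of tolerability but no rate with a denominator for non-serious reactions, by session part or overall.

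Its size can only be illustrated. At assumed rates of 5% and 10%, 40 treated participants would show at least one event with probability 0.87 and 0.985, and zero events would bound the rate below 7.2% (one-sided 95%). These figures assume that all 40 attend and are asked. They show what would be gained by counting, not an error in any stated number: the sample size, the progression interval and the planned analyses are unaffected. This is an inexpensive improvement that should be made, not a flaw that undermines the trial.

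**What to change.** - In Adverse event reporting, state that all adverse events are recorded regardless of seriousness. The reporting and pause provisions for serious events are outside this point.
- Add to the questionnaire that treated participants already complete after each session at t2 and t3 one or two fixed items on discomfort and distress during the session, and a field for whether the session was stopped early (yes/no, with the reason if given). Keeping the reason optional respects the participant's freedom to leave without explanation.
- Report the number affected and the number asked for SH and PFM separately, with 95% confidence intervals, next to the acceptability results that inform Table 2.

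If the full protocol or ethics file already logs non-serious events, the article's wording should be aligned with it, and only the fixed items and the reporting need to be added.

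The cost is about one minute per VR session, slightly more data entry and one more descriptive table. No treatment rule or stated statistic changes.

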### Safety protocol

Participants are asked to answer questions regarding suicidal ideation, as such a safety protocol was developed to ensure that any participant who presents as at risk for suicide receives adequate care. As a part of the study procedure, participants will respond to a self-report version of the C-SSRS for research. Immediately following completion of the questionnaires, the experimenter—who is a trained therapist—will review participant responses and confirm answers to the C-SSRS, using the full baseline/screening version of the measure. If a participant reports suicidal ideation, the experimenter will review the additional suicidal ideation intensity questions and suicidal and nonsuicidal self-injury behavior items with the participant. Following a review of participant answers, the experimenter will then complete a Safety Planning intervention with the participant in lieu of the Coping Plan intervention. The Safety Planning intervention is currently the best practice for responding to suicidal ideation. Participants will be given a copy of the plan to take home and (all participants) will be provided with a resource sheet of local and national mental health resources. Participants will be encouraged to consult their plan and the resource sheet. In the case of suicidal ideation, participants will be offered consultation with a licensed clinical psychologist, who is consulting on the study. In the case of significant risk (as deemed by the experimenter), the licensed clinical psychologist will be contacted for consultation on how to proceed. All risk procedures will be documented in the participant’s study file. The experimenters will not be made aware of whether participants chose to pursue subsequent mental health services. In the unlikely case of an acute mental health crisis in the lab, participants are informed through the consent that the experimenter may call emergency services to ensure they receive the best care possible.

### Data safety and participant confidentiality

All data collected will be stored and scientifically analyzed in accordance with data protection laws (EU General Data Protection Regulation, Federal Data Protection Act [German Bundesdatenschutzgesetz]).

Participant responses will be completely anonymized from the beginning of the study. Upon consenting, participants are given a participant ID, and this number will be used to identify and group their data across timepoints. Responses are never directly linked to participant names or other identifying information. All anonymized data will be stored in a password-protected file on an encrypted server. Recordings, which may be considered to be personal identifiers, will be stored separately from the anonymized data in a password-protected file on an encrypted server. Participants’ paper files—i.e., a copy of their coping plan, the C-SSRS follow-up, any other notes – will be stored securely in a locked filing cabinet in a locked office in the lab. Only the investigators and experimenter will have access to any of these data files. All data will be backed up onto two password-protected and encrypted hard drives, which will be kept in locked cabinets in separate offices belonging to the investigators.

Participants will be offered a copy of the recordings taken during the sessions to take home with them, which they are free to refuse. Participants are made aware through the informed consent and reminded during the session that if they choose to take home the recording, they assume responsibility for keeping it private.

#### Modification and dissemination

Any modifications made to the intervention will be reported to the ethics committee promptly. It is intended that the results from this trial will be reported and disseminated locally, at the institute level, as well as at national and international conferences, and through publication in scientific journals. This trial is intended to inform further iterations of the intervention and the potential and procedure of a subsequent full-scale RCT.

#### Potential implications

This study has implications in both clinical and cognitive psychology. To our knowledge, this is the first study to investigate the potential use of virtual reality as a therapeutic tool in a population of individuals with depression and the first study to investigate the utility of virtual reality as a medium through which to enhance the subjective quality of future thought in any clinical population.

The findings have the potential to inform the development of novel interventions for depressed and suicidal young adults and novel prevention techniques for young adults at risk for developing depression and suicidal ideation. This study will provide evidence as to the feasibility and acceptability of implementing a virtual reality-based intervention among young adults experiencing depression.

Further, although this pilot study is not powered to detect effects of clinical outcomes, results will guide the development of a full-scale RCT. Results of a well-powered study will provide valuable insights on the cognitive processes (e.g., executive functioning, remembering, etc.) involved in future thinking and evidence as to whether virtual reality can provide scaffolding for deficits in those cognitive processes among individuals with depression.

## Data Availability

Not applicable.

## Abbreviations

AIM: Acceptability of Intervention Measure
BDI-II: Beck Depression Inventory-II
BRIEF-A: Behavior Rating Inventory of Executive Function for Adults
CONSORT: Consolidated Standards of Reporting Trials
C-SSRS: Columbia–Suicide Severity Rating Scale
FIM: Feasibility of Intervention Measure
FS: Future Self
FU-MH: FutureU for Mental Health
GSES: General Self-Efficacy Scale
IAM: Intervention Appropriateness Measure
LGCM: Latent Growth Curve Modeling
OSF: Open Science Forum
PANAS: Positive and Negative Affect Scale
PFM: Positive-Future Memories Intervention
PHQ-9: Patient Health Questionnaire-9
PIT: Prospective Imagery Task
PS: Present self
RCI: Reliable Change Index
RCT: Randomized controlled trial
SAE: Serious adverse event
SH: Self-help intervention
SI: Suicidal ideation
SPIRIT: Standard Protocol Items: Recommendations for Interventional Trials
SUSAR: Suspected Unexpected Serious Adverse Reactions
TAU: Treatment as Usual Control Group
TX: Treatment Group
VE: Virtual environment
VR: Virtual reality
